## **5.3 Informed Consent**

Consent forms describing in detail the study intervention, study procedures, and risks are given to the participant and written documentation of informed consent is required prior to starting intervention/administering study intervention. The consent materials are submitted with this protocol:

- Consent form

### **5.3.1 Screening (if applicable)**

Not applicable

### **5.3.2 Recruitment, Enrollment and Retention (if applicable)**

Potential subjects will be identified by reviewing clinic patients with the provider and patients will be targeted for in-person recruitment by the treating provider with the trained research assistant present. We may contact patients of treating providers who have given written agreement to have their patients who are eligible for PFR to be contacted if unable to consent in person. The study will be introduced to the patients by the treating provider and the trained research assistant will consent and complete initial survey administration during the initial visit, or if not able will complete the survey via telephone call or electronic communication. Patients will be compensated a total of \$50 for attendance of the first and last in-person PFMT sessions.

### 5.3.3 Study Visits (is applicable)

1. Initial clinic visit
  - a. SF-12
  - b. And one of the following surveys:
    - i. CCIS
    - ii. PAC-SYM
    - iii. ICIQ-SF
    - iv. POP-SS
2. In person visit with pelvic floor therapist (1 hour)
  - a. Introduction to PFMT clinical visit by a certified pelvic floor therapist
  - b. Graded evaluation of pelvic floor exercises on a scale of 1-3 ( 1= cannot replicate in any meaningful way, 2 = partially, 3 = fully perform)
3. Midway check-in with research team member (15 minutes)
  - a. Elicit feedback on self-direct video-based training
  - b. Completion of SUS
4. Completion in person visit clinical visit with pelvic floor therapist (1 hour)
  - a. Graded evaluation of pelvic floor exercises on a scale of 1-3 (1= cannot replicate in any meaningful way, 2 = partially, 3 = fully perform)
5. Completion survey within 1 week of seeing pelvic floor therapist
  - a. SF-12
  - b. And one of the following surveys:
    - i. CCIS
    - ii. PAC-SYM
    - iii. ICIQ-SF
    - iv. POP-SS
  - c. SUS

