## 2.3 Potential Risks and Benefits

### 2.3.1 Potential Risks

#### Pelvic Floor Muscle Therapy Sessions (in-person):

Participating in PFMT can be time consuming and may be uncomfortable for some patients. There is no guarantee that the instruction and exercises in these sessions will prevent patients from having persistent or worsening pelvic floor dysfunction. A trained physical therapist will be supervising and teaching these sessions. Patients can opt out of certain exercises if desired.

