## 4 Study Design

### 4.1.1 General Design Description

Patients will be enrolled during the clinic visit when they are initially referred for PFR. It will be explained that they are forgoing standard of care of all in-person pelvic floor rehabilitation and will complete the initial survey at this time. They will then have an introductory session with a pelvic floor therapist to assess their baseline function, which does not differ from the standard of care other than the pelvic floor therapist using a graded scoring system to assess exercise completion ability. This initial visit will be prioritized as the waitlist for pelvic floor rehabilitation can be up to 6 months. Then they will complete the 8 weeks of remote, self-directed video-based PFMT. At the midway point after completing 4 weeks of the remote, self-directed video based PFMT, patients will be contacted by a member of the research team to elicit feedback and complete a system usability scale to evaluate patient perspective of the online training program. After this period, they will have another in-person session with the same pelvic floor physical therapist to assess ability to complete exercises successfully with the same graded scoring system. They will then complete a system usability scale survey and repeat the initial surveys for QoL and symptom surveys within 2 weeks of the final in person pelvic floor therapist appointment.

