## **5.2 Study Schedule**

Initial surveys completed at initial clinic visit

In person visit standard of care visit with pelvic floor therapist and graded scoring of exercise completion ability (1 hour)

8 weeks of online, video-based PFMT program; videos were created by Yale (website: <https://pelvicfloorthrapy.wixsite.com/yale-video-based-pel>)

Midway check-in with research team and completion of SUS survey (15 minutes)

Completion in person standard of care visit with pelvic floor therapist and graded scoring of exercise completion ability (1 hour)

Completion surveys after 8 weeks of video-based PFMT (within 1 week of in person visit)

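### The completion SUS, SF-12 and symptom surveys follow the final therapist visit and are timed from it, so scores meant to describe the video course can be coloured by therapist contact and fall at no fixed time after week 8

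*Protocol*

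**What the plan says.** **Order.** Protocol section 4.1.1 puts the final in-person session after the 8 video weeks and continues: "They will then complete a system usability scale survey and repeat the initial surveys for QoL and symptom surveys within 2 weeks of the final" in-person appointment. Sections 5.1 and 5.3.3 list the same sequence, visit first and surveys second.

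**Window.** Section 5.3.3 has "Completion survey within 1 week of seeing pelvic floor therapist". Section 5.2 has "Completion surveys after 8 weeks of video-based PFMT (within 1 week of in person visit". Section 4.1.1 allows 2 weeks. All three count from the visit. No section gives a maximum interval from week 8 to the visit.

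**Nature of the final visit.** Section 4.1.1 gives its purpose as "to assess ability to complete exercises successfully with the same graded scoring system". Section 5.2 calls it "Completion in person standard of care visit with pelvic floor therapist and graded scoring of exercise completion ability (1 hour", section 5.3.2 pays patients for it as a PFMT session, and section 5.4.1 plans a pre-post comparison of the supervision and cueing that patients need. Of in-person sessions in general, section 2.3.1 says: "A trained physical therapist will be supervising and teaching these sessions".

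**Use of the scores.** Section 4.2.1 makes the SUS a primary outcome. Section 5.1.1 treats it as usability of the video application and the change in SF-12 and symptom scores as efficacy of video-based PFMT. Hypothesis B (section 3.1) and the secondary objective (section 3.3) use the same attribution.

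**The concern.** A usability rating of a website, and a patient's report of symptoms and quality of life, are open to what happened just before they were given. Here that is an hour with the therapist who grades the patient's exercises. The trial has one arm, so no comparator shares that contact and its influence cannot be subtracted.

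The timing is a second problem. The survey clock starts at a visit whose own date is not tied to week 8, so patients can be measured at different distances from the end of the course. With 10 to 20 patients, a few late visits can noticeably change what the post score represents.

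**Working it through.** The protocol states no figure to reproduce here; its sample size of 10 to 20 has no formula behind it. The check is one of order, timing and content.

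**1. Who is affected.** Section 5.4.6 excludes anyone who does not attend both in-person visits. Every analysed patient therefore has a final visit, and under the stated order every analysed completion score follows it. Section 5.2 alone could be read as allowing a survey shortly before the visit, but the sequence in section 4.1.1 and the numbering in sections 5.1 and 5.3.3 settle the order.

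**2. When the post surveys fall.** Let *w* be the weeks from the end of the course to the final visit. The protocol does not give *w*; the values below are assumptions.

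- Earliest survey, counted from the start of the videos: 8 + *w*
- Latest survey: 8 + *w* + 1 (sections 5.2 and 5.3.3) or 8 + *w* + 2 (section 4.1.1)

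| *w* (assumed) | 1-week window | 2-week window |
|---|---|---|
| 0 | weeks 8–9 | weeks 8–10 |
| 2 | weeks 10–11 | weeks 10–12 |
| 4 | weeks 12–13 | weeks 12–14 |

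If some patients have *w* = 0 and others *w* = 4, completion scores in one analysis could lie up to 14 − 8 = 6 weeks apart. A survey returned 10 days after the visit is on time under section 4.1.1 and late under sections 5.2 and 5.3.3.

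**3. What precedes the scores.**

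- Completion SUS: the final visit comes first. The week-4 SUS (sections 4.1.1, 5.2 and 5.3.3) does not have this problem, but covers only half the course.
- SF-12 and symptom surveys: the final visit comes first, and there is no intermediate time point.
- Baseline surveys: completed at the clinic visit, before the first therapist session. The pre-post change therefore spans both in-person sessions. Moving the completion surveys ahead of the final visit removes the second session only.

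**4. Sensitivity, not an estimate.** Suppose nothing except the final visit moves SF-12, and that it shifts the mean change by *d* standard deviations of the change. The chance that a paired t-test rejects (two-sided 0.05, also assumed, since section 5.4.1 states no level) follows a noncentral t with n − 1 degrees of freedom and noncentrality *d*√n.

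| *d* (assumed) | n = 10 | n = 20 |
|---|---|---|
| 0.1 | 5.9% | 7.1% |
| 0.2 | 8.8% | 13.6% |
| 0.3 | 13.6% | 24.7% |
| 0.5 | 29.3% | 56.5% |

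The protocol says nothing about *d*. The table shows only that a modest shift would be enough to matter. Each symptom scale is completed by only some of the patients, so these sample sizes fit SF-12 alone.

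**The case against.** **The final visit is an assessment.** Section 4.1.1 gives that purpose, and section 5.3.3 lists an introduction to PFMT only at the first visit. This stands in part. A reader might infer that the post scores contain a second course of treatment; the text does not establish that, and the remark about supervising and teaching is a general risk statement. But sections 5.2, 5.3.2 and 5.4.1 describe more than silent measurement, and grading alone can colour a rating given days later.

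**The package is hybrid.** The synopsis includes both in-person sessions and section 1.1 asks about a hybrid approach. On that reading the final session belongs to the intervention. The objectives, Hypothesis B and section 5.1.1 speak of video-based PFMT, so the wording needs reconciling. The unfixed time point remains on either reading.

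**The fix does not isolate the videos.** Correct. The first session stays in the change, and a single-arm pre-post design cannot attribute the change to the videos under either order.

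**The SUS already has a clean reading at week 4.** Correct, and it softens the point for the primary outcome.

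**Long waits are speculative.** A reader might infer delays of 10 weeks or 6 months. The 10 weeks in section 1.2 run from referral to first session. Section 4.1.1 cites the long waitlist to explain why the first visit is brought forward: "This initial visit will be prioritized as the waitlist for pelvic floor rehabilitation can be up to 6 months". Neither describes a return visit by an enrolled patient. Section 6.11 also ends follow-up by August 30 2026, though that is a loose limit for early enrolees. What stands is that no interval is set, not that a long one is expected.

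**Conclusion.** The point holds as a design weakness worth correcting. The order and the visit-based clock are explicit, they affect the completion SUS, SF-12 and symptom scores of every analysed patient, and the two stated windows contradict each other. The scores are open to response bias from therapist contact and are taken at a time that varies with the date of the visit.

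The direction and size of any bias are unknown, and the timing spread depends on an assumed wait. The therapist's graded score is taken at the visit itself and is not affected. Nothing here shows that the feasibility result would be invalid; the case for changing the order is that the weakness is avoidable at almost no cost.

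**What to change.** In sections 4.1.1, 5.1, 5.2 and 5.3.3:

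- Anchor the completion SUS, SF-12 and symptom survey to the end of week 8 and require them before the final visit. Send them through Qualtrics, which section 5.1.1 already provides for; anyone who has not answered completes them on arrival, before the therapist sees them.
- Replace the 1-week and 2-week windows with a single window counted from week 8.
- Record the days from the last video to each post measurement, including the therapist's grading, and report their spread.
- Reconcile the synopsis and section 1.1 with sections 3.1, 3.3 and 5.1.1 on whether the scores describe the videos or the hybrid package, and acknowledge that the first in-person session lies inside the pre-post change.

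Cost: one reminder at week 8 and edits to sections whose conflicting windows need correcting anyway. No visit, questionnaire or member of staff is added, and the scheduling of the final visit need not change.

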## 5.4 Statistical Method

### 5.4.1 Statistical Design

Demographic information will be reported using descriptive statistics. Categorical variables will be analyzed with chi-squared test and continuous variables will be analyzed with Wilcoxon Rank sum test. Paired T-test will be used to evaluate differences pre and post treatment of the following measures:

- 1) amount of supervision and cues needed by the pelvic floor therapist
- 2) difference in graded scoring of exercises by the pelvic floor therapist
- 3) CCIS scores
- 4) PAC-SYM score
- 5) SF-12 Scores
- 6) ICIQ-SF Scores
- 7) POP-SS Scores

### 5.4.2 Sample Size Considerations

This is a feasibility study with no prior literature publishing on the use of video-based PFMT. Based on prior feasibility studies, the sample size will be between 10-20 patients.

### 5.4.3 Planned Analyses

The primary analysis to evaluate for feasibility and safety will involve the percentage of patients who successfully learned PFMT, analysis of incidence of adverse events and overall score of usability for the web-based videos. We will also evaluate the ability of participants to successfully complete the exercises based on the graded scoring by the pelvic floor therapists. Analysis of secondary outcomes

related to symptom improvement and quality of life will analyze SF-12, CCIS, PAC-SYM, ICIQ-SF and POP-SS scores.

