# 1 Background/Literature Review

## 1.1 Background

Pelvic floor rehabilitation (PFR) is a group of therapeutic techniques used to help patients with pelvic floor dysfunction, such as urinary incontinence or fecal incontinence. The exercises commonly use in PFR include pelvic floor muscle therapy (PFMT) with biofeedback training, rectal balloon training or electrical stimulation. Together, these techniques aim to improve the strength, tone and endurance of the pelvic floor musculature and sphincter complex. For fecal incontinence, they have shown to decrease symptoms ranging between 50-80%. A meta-analysis looking at 18 trials utilizing PFMT for urinary incontinence found an improvement in symptoms in all studies.

Despite PFMT being shown to be efficacious for numerous different pelvic floor dysfunction disorders, less than 50% of patients referred are compliant with the recommend duration of treatment. Previous studies found that inconvenience, cost, lack of knowledge and discomfort around the concept of PFMT are all reasons why patients may have poor compliance. Patients have shown a positive reception to telehealth-based PFMT visits. It is not known if a hybrid approach to PFMT including both in-person and video-based training videos may help to alleviate some of these barriers while providing the same adequate amount of guidance, improvement in symptoms and QoL for patients. Thus, the purpose of this study is to evaluate the feasibility and acceptability of a web-accessible 8-week video-based PFMT for pelvic floor disorders.

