## 2.2 Purpose of Study/Potential Impact

Evaluating the feasibility and safety of video-based PFMT will allow us to determine if this video-based training could be offered as a treatment alternative for patients with pelvic floor dysfunction.

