**2.3.2 Potential Benefits**

**Short term:** Patients may have improvement in pelvic floor dysfunction and QoL

**Long term:** Patients may have improvement in pelvic floor dysfunction and QoL. If successful, the videos could be developed into a mobile based application and offered as an alternative treatment method.

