**3.2 Primary Objective**

The primary objective is to determine the feasibility and accessibility of using a video-based PFMT for patients with pelvic floor dysfunction.

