## 4.2 Outcome Variables

### 4.2.1 Primary Outcome Variables

SUS, percentage of video completion, change in the graded evaluation of exercises by pelvic floor therapist pre and post intervention, adverse events

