#### **5.4.5 Interim Analysis (if applicable)**

#### **5.4.6 Handling of Missing Data**

Patients who complete less than 75% of the videos or do not attend both initial and final in person pelvic floor therapy visit will be excluded from the study. A complete case analysis will be performed for patients who have completed between 75-100% of the videos.

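### The protocol sets out to determine feasibility, but no primary measure has a success criterion, and non-completers are excluded instead of counted as feasibility failures

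*Protocol*

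**What the plan says.** **Aim.** Section 3.2 states: "The primary objective is to determine the feasibility and accessibility of using a video-based PFMT". Section 2.2 says that evaluating feasibility and safety "will allow us to determine if this video-based training could be offered as a treatment alternative". Section 2.3.2 adds: "If successful, the videos could be developed into a mobile based application and offered as an alternative treatment method".

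**Primary measures.** Section 4.2.1 lists "SUS, percentage of video completion, change in the graded evaluation of exercises by pelvic floor therapist pre and post intervention, adverse events". Section 5.4.3 describes the primary analysis differently: "The primary analysis to evaluate for feasibility and safety will involve the percentage of patients who successfully learned PFMT", plus adverse-event incidence and the overall usability score. It adds an evaluation of exercise ability from the therapist's grades. None of these has a target, a bound or a tolerable rate. Section 5.3.3 defines the 1-3 grade, with 3 meaning full performance, but gives no rule that turns grades into a patient who has learned PFMT.

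**Tests.** Section 5.4.1 states: "Paired T-test will be used to evaluate differences pre and post treatment of the following measures". Of the seven measures that follow, only the change in therapist grade is also a primary outcome in 4.2.1. The section names chi-squared and Wilcoxon rank sum tests too, but ties them to no primary measure.

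**Who is analysed.** Under section 5.4.6, "Patients who complete less than 75% of the videos or do not attend both initial and final in person pelvic floor therapy visit" are excluded from the study, and a complete case analysis is done on those with 75-100% of the videos.

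**Sample size.** Section 5.4.2 gives 10-20 patients by analogy with other feasibility studies, with no target rate or precision.

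**The concern.** A study that sets out to determine something needs a statement of which results would count for it and which against. Here that statement is absent for every primary measure, and it cannot be recovered from the sample size, which rests on no target. In an open single-arm study, a pass mark chosen once results are known cannot be chosen neutrally.

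The exclusion in 5.4.6 makes this worse. Failing to get through the videos, or not returning for the final visit, is the plainest sign that a remote programme is not feasible. The protocol treats those patients as missing data and removes them. Read literally, this conditions video completion, a listed primary outcome, on already being at least 75%, and computes the percentage who learned PFMT among the patients most likely to have learned it.

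At stake is the conclusion in 2.2 that the videos could be offered in place of in-person therapy. Section 1.1 motivates the study by poor compliance with referred therapy ("less than 50% of patients referred are compliant with the recommend duration of treatment"), and the plan removes the patients who would show whether video delivery does better.

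**Working it through.** The protocol has no figure to reproduce: 10-20 patients is given without alpha, power, effect size, target rate or precision. The calculations below show what the missing criterion and the exclusion can do.

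**1. Effect of the denominator.** Inputs: n=20 (upper end, 5.4.2) and the exclusion rule (5.4.6). Assumed: 90% of those analysed are judged to have learned PFMT, and nobody excluded is counted as having learned.

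| Enrolled patients meeting the 5.4.6 rule | Analysed | Learned, of analysed | Learned, of enrolled |
|---|---|---|---|
| 40% | 8 | 90% | 0.40 × 0.90 = 36% |
| 50% | 10 | 90% (9/10) | 0.50 × 0.90 = 45% (9/20) |
| 60% | 12 | 90% | 0.60 × 0.90 = 54% |

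The reported 90% is the same in every row. Video completion among those analysed is at least 75% whatever happened in the full group.

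**2. Dependence on an unstated pass mark.** Assume a true completion rate of 50%, the ceiling of the compliance figure in 1.1. The chance of meeting a mark is P(X ≥ k), with X ~ Binomial(n, 0.50) and k the smallest count at or above the mark.

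| Mark | n=20 | n=10 |
|---|---|---|
| 50% | k=10: 0.588 | k=5: 0.623 |
| 60% | k=12: 0.252 | k=6: 0.377 |
| 70% | k=14: 0.058 | k=7: 0.172 |
| 75% | k=15: 0.021 | k=8: 0.055 |

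**3. What the paired t-test can show.** Illustration with n=20: 8 patients move from grade 1 to 2, and 12 stay at 1.
- Mean change = 8/20 = 0.40.
- SD = √[(8 × 0.60² + 12 × 0.40²)/19] = √(4.80/19) = 0.503.
- t = 0.40/(0.503/√20) = 3.56 on 19 df, two-sided p = 0.002.

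The change is clearly significant, yet no patient reaches grade 3.

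**4. Safety precision.** With zero events, the one-sided 95% upper bound is 1 − 0.05^(1/n): 0.259 at n=10 and 0.139 at n=20.

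**5. A workable criterion.** Count every enrolled patient. Success is at least 75% of videos plus both therapist visits (the cut-offs in 5.4.6). Require the one-sided 95% exact (Clopper-Pearson) lower bound L, which solves P(X ≥ k | n, L) = 0.05, to exceed 0.50.

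| n | Not enough | Enough | Chance of passing if true rate is 50% | Chance if true rate is 80% (assumed) |
|---|---|---|---|---|
| 20 | 14/20, L=0.492 | 15/20, L=0.544 | 0.021 | 0.804 |
| 15 | 11/15, L=0.489 | 12/15, L=0.560 | 0.018 | 0.648 |
| 10 | 8/10, L=0.493 | 9/10, L=0.606 | 0.011 | 0.376 |

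**The case against.** The strongest reply is that this is a pilot. Much of its language is about evaluating and assessing, sections 2.2 and 2.3.2 speak only of what could follow, and estimates with confidence intervals would be an acceptable product. An unseen SAP may also hold thresholds. Part of this stands: nothing here calls for a power calculation or a larger study. But section 3.2 says determine, not estimate, and the protocol itself fixes the primary analysis and the exclusion. Criteria in a SAP would not undo the exclusion in 5.4.6 as written.

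It can also be said that 5.4.6 sits under missing data and that the number excluded would be visible in any report. That is likely, but the text gives no primary measure in which those patients count.

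Several stronger readings should be resisted:
- A reader might infer that the t-test decides feasibility. Section 5.4.3 does not say so, and it commits separately to looking at exercise ability, where the pattern in step 3 would show. The all-at-grade-1 baseline there is invented for illustration.
- A reader might infer that zero change is the only hypothesis tested anywhere. Section 5.4.1 names other tests; the accurate statement is that no other test is tied to a listed primary outcome.
- A reader might infer that almost any result would be called feasible, or that the plan can never return a negative answer. The protocol does not say this. A plan with no rule fixes neither answer.
- A reader might take 50% as the protocol's own benchmark. Section 1.1 describes referred patients' compliance with a recommended treatment duration. Here patients have consented, get a prioritised first visit and are paid for both in-person visits, so the figure is not like-for-like.

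**Conclusion.** The point holds in this form: the protocol aims to determine feasibility without a success criterion for any primary measure, the test attached to therapist grade answers a different question, and the exclusion rule removes feasibility failures from the analysis.

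The exclusion is the most concrete part. It can turn 45% of enrolled patients into a reported 90%, given the assumed 50% completion and 90% learning among completers. The missing criterion leaves the conclusion open: with a true completion rate of 50%, the chance of passing runs from 59% to 2% at n=20 and from 62% to 5% at n=10, across marks of 50% to 75%. That the chance varies with the mark is true of any study; what matters here is that no mark is fixed. Likewise, the zero-event bounds of 26% and 14% are generic to the sample size, and matter only because 2.2 draws a safety conclusion.

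The 50% and 80% true rates, the learning proportion and the grade pattern are assumptions. The exclusion, the missing criteria and the null of zero change are read directly from the protocol.

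**What to change.** 1. **Section 5.4.3:** before data review, fix a feasibility criterion counted over all enrolled patients. One workable example is to conclude feasibility if the one-sided 95% exact lower bound, for the proportion who complete at least 75% of the videos and attend both therapist visits, exceeds 50% (at least 15/20, 12/15 or 9/10). The 50% is illustrative; the sponsor may set another mark, provided it is set in advance.
2. **Section 5.4.6:** amend so that non-completers and those who miss a therapist visit count as failures for the feasibility measures. A complete case analysis can remain for the symptom and quality-of-life scores.
3. **Supporting measures:** report the percentage who learned PFMT, also over all enrolled and with a stated patient-level definition, and SUS, therapist grades and adverse events, with exact or 95% confidence intervals. State that the t-test on grade change does not determine feasibility.
4. **Section 2.2:** limit the safety statement to the observed adverse-event rate with its upper bound.

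**Cost.** Short text changes in three sections through an IRB amendment, with no extra visits or data and no change to the planned 10-20 patients. The study can then fail its criterion: with an assumed true rate of 80%, the example rule is met 80% of the time at n=20 but only 38% at n=10, which favours recruiting towards 20. If that is too strict at small n, the alternative is to report the estimate over all enrolled with its confidence interval and restate the objective in 3.2 as estimating feasibility.
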